## Abstract

Musculoskeletal conditions represent a considerable burden worldwide, and are predominantly managed in primary care. Evidence suggests that many musculoskeletal conditions share similar prognostic factors. Systematically assessing patient’s prognosis and matching treatments based on prognostic subgroups (stratified care) has been shown to be both clinically effective and cost-effective. This study (Keele Aches and Pains Study) aims to refine and examine the validity of a brief questionnaire (Keele STarT MSK tool) designed to enable risk stratification of primary care patients with the five most common musculoskeletal pain presentations. We also describe the subgroups of patients, and explore the acceptability and feasibility of using the tool and how the tool is best implemented in clinical practice. The study design is mixed methods: a prospective, quantitative observational cohort study with a linked qualitative focus group and interview study. Patients who have consulted their GP or health care practitioner about a relevant musculoskeletal condition will be recruited from general practice. Participating patients will complete a baseline questionnaire (shortly after consultation), plus questionnaires 2 and 6 months later. A subsample of patients, along with participating GPs and health care practitioners, will be invited to take part in qualitative focus groups and interviews. The Keele STarT MSK tool will be refined based on face, discriminant, construct, and predictive validity at baseline and 2 months, and validated using data from 6-month follow-up. Patient and clinician perspectives about using the tool will be explored. This study will provide a validated prognostic tool (Keele STarT MSK) with established cutoff points to stratify patients with the five most common musculoskeletal presentations into low-, medium-, and high-risk subgroups. The qualitative analysis of patient and health care perspectives will inform practitioners on how to embed the tool into clinical practice using established general practice IT systems and clinician-support packages.

## Background

Musculoskeletal conditions represent a considerable burden worldwide. The Global Burden of Disease study findings show that such conditions as low-back pain are the leading cause of years lived with disability in Western Europe and Australia, and that musculoskeletal conditions overall account for 6.8% of global disability-adjusted life-years, comparable to cancer (7.8%), ischemic heart disease (5.2%), and mental disorders (7.4%).^1^ This burden is reflected in health care use: musculoskeletal consultations account for around a fifth of all consultations in UK primary care.^2^,^3^ Prevalence of persistent musculoskeletal pain is high, estimated at 25%–32%,^4^ and recurrence is common.^5^ Musculoskeletal conditions thus have a major impact on the individual, health care, and society.^6^

While regional musculoskeletal pain presentations (ie, pain specific to a certain body region) are recognized by virtue of the anatomical location (eg, back, neck, shoulder, knee) and associated features of such pain presentations (ie, impact on physical function), there is strong substantive evidence that pain presentations share common underlying mechanisms.^7^ Co-occurrence of pain in different body regions is high,^8^ and risk of poor outcome is increased for those with multisite pain.^9^,^10^ Additionally, patients with different regional musculoskeletal pains (eg, back, neck, shoulder, or knee pain) and those with multisite pain share similar prognostic factors.^11^–^13^ Previous work has demonstrated that a chronic pain-risk score, incorporating prognostic indicators, and developed in patients with back pain,^14^ is valid for use among patients with pain at different anatomical sites, and in different settings.^15^–^17^ Other work^18^ has shown that patients can be screened to assess the presence of prognostic factors, irrespective of the specific location of the musculoskeletal condition. However, previous methods and tools, such as the Örebro Musculoskeletal Pain Screening Questionnaire were not designed for use specifically within primary care^19^,^20^ or to stratify patients based on their level of risk and recommend matched treatments (stratified care). One model of stratified care is to create subgroups based on a prognostic profile.^21^ This approach of stratified care can “fast-track” patients to the appropriate treatment by supporting clinical decision making, and has the potential to maximize treatment benefit, reduce harm, and increase health care efficiency.^22^

One prognostic tool (the STarT [subgroups for targeted treatment] Back tool) was successfully developed for low-back pain patients in primary care,^23^ specifically to assist in matching patients to different treatments. The tool consists of nine items, and utilizes cutoff point scores to identify three prognostic subgroups (low, medium, and high risk of persistent back-related physical disability). All physical and psychological prognostic indicators in the STarT Back tool were chosen based on their potential to be modifiable through treatment. Subsequent use of the tool, as part of a stratified care model in which subgroups of patients were matched to different treatments, has demonstrated superior clinical and economic outcomes compared to best current practice and usual primary care.^24^,^25^

Given this promising research, the predictive ability of a modified, generic version of the STarT Back tool was tested in a broader range of patients with musculoskeletal pain presentations (neck pain, upper-limb pain, lower-limb pain, multisite pain, and back pain). The predictive performance of this new draft – “Keele STarT MSK tool” – was assessed in secondary analysis of two large data sets of patients with musculoskeletal pain conditions consulting physiotherapy services (PhysioDirect study)^26^ and musculoskeletal primary–secondary care-interface services (SAMBA study).^27^ Results showed a moderate-to-good level of predictive ability of the draft tool in the identification of patients who developed persistent disabling pain, eg, prediction of poor outcome using area under the curve (AUC) – back pain AUC 0.72, 0.79, neck pain AUC 0.82, 0.88, upper-limb AUC 0.79, 0.86, lower-limb AUC 0.79, 0.86, and AUC 0.83, 0.82 multisite pain – in PhysioDirect and SAMBA, respectively. However the results also indicated that different optimal cutoff points were required for different regional pain presentations (eg, lower limb, upper limb, spinal pain). Subsequent informal discussions on the applicability of the draft tool were carried out with GPs and first-contact health care practitioners (HCPs). Feedback from discussions indicated that due to the complexities of scoring the draft tool (ie, different cutoff points per body region) added to the current time pressures within primary care, a single generic tool with one set of cutoff points would be preferable in clinical practice. Furthermore, a more straightforward tool would facilitate links to matched treatments within a stratified care model.

The overall aims of the Keele Aches and Pains Study (KAPS) are further to refine and validate the draft Keele STarT MSK tool, and based on our previous experience in implementing stratified primary care for patients with low-back pain^25^ to collect information about the anticipated acceptability and feasibility of using such a tool, as well as identify barriers to implementation and practical solutions to these barriers.^28^ We aim to develop the tool for use with patients who have the five most common musculoskeletal pain presentations in primary care: back, neck, shoulder, knee, or multisite pain.^3^ The KAPS forms part of a larger National Institute for Health Research (NIHR) program of four linked work packages. The overall objective is to stratify patients with a range of musculoskeletal presentations based on risk of poor outcome, identify treatment options that are matched to each stratum, test the acceptability of this model in primary care, test whether such an approach is effective in the improvement of patient outcomes and experience, and test whether it is cost-effective.

### Aims and objectives

Within the context of primary care and the five most common musculoskeletal presentations, there are two key aims of the KAPS: 1) to refine and externally validate the draft Keele STarT MSK tool, and 2) to explore how such a tool might best be implemented within clinical practice. Specific objectives include:
refine the Keele STarT MSK tool based on face, discriminant, construct, and predictive validitydetermine the tool risk-strata cutoff points based on optimal predictive values and suitability for matched treatment optionsestimate the proportions of patients classified at low, medium, and high risk of poor outcome and describe their characteristics, including patient health care utilization and costs and health-related quality of lifeexamine the validity of a refined tool (predictive, external validation)explore clinicians’ perspectives on the acceptability and “added value” of stratified care based on prognosis compared to current primary care management of patientsexplore patients’ perspectives about stratified primary care based on prognosis (eg, patient subgrouping using the tool, matched treatment options)identify clinicians’ and patients’ perceived barriers and solutions to using the draft Keele STarT MSK tool and matched treatment options in clinical practice.

## Methods/design

Ethical approval for this study has been granted by the South East Scotland Research Ethics Committee in the UK (14/SS/0083).

### Study design and setting

This will be a prospective observational cohort study with a linked qualitative study within a primary care setting.

### Participating patients

Consecutive adult patients who visit their GP with one (or more) of the five most common musculoskeletal pain presentations – back, neck, shoulder, knee, or multisite pain – will be invited to participate in the cohort study. A subsample of patients who respond and agree to participate in the cohort study will be invited to take part in the linked qualitative focus groups and interviews. In addition, GPs and other HCPs involved in musculoskeletal treatments (eg, physiotherapists) will be invited from the participating general practices and related services, or known clinical networks, to take part in focus groups and interviews.

### Inclusion/exclusion criteria

Inclusion criteria are patients registered at participating general practices, aged 18 years or over, consulting with the included musculoskeletal pain presentations, and able to read and understand English. All consecutive patients will be invited to participate, regardless of prior consultations. Exclusion criteria are indication of serious pathology (eg, suspected fracture, cancer), inflammatory arthritis, crystal disease, spondyloarthropathy, polymyalgia rheumatica, pregnancy-related pain problems, urgent cases (eg, cauda equina syndrome), or vulnerable patients (eg, experienced recent trauma, cognitive impairment, dementia, or terminal illness). There are no inclusion/exclusion criteria for the GP and other HCP focus groups and interviews, but researchers will attempt to recruit to maximize sample variation on the basis of age, sex, clinical experience, location, and clinical specialty. All focus groups will be conducted in English.

### Cohort study recruitment

Individual patients who consult with back, neck, shoulder, knee, or multisite pain will be identified through relevant musculoskeletal symptom and diagnostic Read codes. The Read codes have been previously used by Jordan et al,^3^ with additional amendments and checks for relevance and completeness carried out by GPs in the research team. GP practice staff and Clinical Research Network staff will support weekly-to-fortnightly electronic record searches for the relevant Read codes at participating primary care practices to identify potentially eligible patients. Patients’ GPs will be invited to screen patient lists prior to mailing. Eligible patients will receive an invitation letter and survey pack (participant information sheet, baseline questionnaire, and prepaid return envelope) from their GP shortly after their musculoskeletal pain consultation (index consultation).

Return of the completed questionnaire by the patient will signify consent to participate in the cohort study (ie, consent to receive further questionnaires), as specified within the participant information sheet. In addition, specific consent will be requested to allow access to patients’ medical records and to be contacted about further linked research (ie, linked qualitative focus groups and interviews). Baseline nonresponders will be sent a reminder postcard after 2 weeks and a reminder letter (with a copy of the baseline questionnaire) 2 weeks after that. Patients who indicate that they do not wish to take part at any point will not be sent any further correspondence. Patients will not receive any payment or financial incentive to take part.

### Cohort study follow-up

All patients who have signified consent to take part will be sent follow-up questionnaires 2 months and 6 months after baseline. Wording on each follow-up questionnaire will be personalized to indicate which anatomical area they originally consulted about during their index consultation (ascertained from patients’ baseline questionnaire responses). One week before follow-up questionnaire mailing, patients will receive a reminder (pre-follow-up) that they are about to receive their next questionnaire. After the 2-month and 6-month questionnaire mailing, nonresponders will receive a reminder after 2 weeks (postcard, text message, or email), and a repeat questionnaire 2 weeks later. After the final 6-month mailing, a brief questionnaire containing only the key-outcome measures (minimal data collection [questionnaire]) will be sent at 6 weeks to nonresponders. Finally, telephone contact will be attempted at 8 weeks for those who have provided a telephone number on their baseline questionnaire, to collect key-outcome data (minimal data collection [telephone]). Telephone calls will be carried out by a research nurse. Please see Figure 1 for a flowchart of the recruitment stages for the KAPS.

The recruitment strategies outlined follow a recent Cochrane review of best practice to increase response to postal questionnaires,^29^ and follow guidelines from the World Health Organization for research to adapt to the rapid changes in the way people communicate (eg, mobile technologies, telephone communication, Internet).^30^

### Cohort study data collection

The draft Keele STarT MSK tool and the key primary quantitative measures will be included in the questionnaire measures at all time points. The key primary quantitative measures are physical health (short-form [SF]-36 version 2 physical component summary score),^31^,^32^ pain-intensity (least, average, and current pain),^33^ and pain interference (Promis pain-interference scale).^34^ The study will also include a measure of health-related quality of life (EuroQol [EQ]-5D-5L)^35^ at all time points. The minimal data-collection questionnaire will include the SF-12, which is a shortened version of the SF-36 version 2.^36^ Secondary measures include aspects of pain duration, spread and bother, self-reported change in symptoms (follow-up stages only), pain catastrophizing, pain self-efficacy, illness perceptions, sleep problems, physical activity, social support, health literacy, comorbidity, employment status, and factors about employment if applicable (see Table 1 for full list of measures, references, and time points for data collection). There will also be questions in the follow-up questionnaires on previous National Health Service (NHS) and non-NHS health care utilization (eg, contact with GP, nurse, physiotherapist, osteopath, and use of X-rays, surgery, prescriptions, over-the-counter medication). In addition, single-item questions derived and adapted from the established measures outlined will be included. The selection of these items is based on their prognostic performance in primary care musculoskeletal pain studies.^37^–^40^

### Cohort study medical record review

For those who give consent, analysis of medical records will supplement patient self-report information (eg, additional information on prescriptions, consultation frequency, referral for further treatment, diagnostic tests, and sickness certification/fit notes). The time scale for medical record review is 1 month prior to the patient’s index consultation, up to 6 months after their index consultation.

### Cohort study sample size

Based on a 6-month recruitment period at each participating practice, from a source population of approximately 40,000 registered adult patients with an estimated annual consultation prevalence of 20% for musculoskeletal consultations,^3^ we estimate that there will be approximately 3,000 eligible patients who consult with the five most common musculoskeletal pain presentations during the recruitment period. With an estimated response of 60%–70% (based on previous studies with similar populations),^33^,^41^ we anticipate recruiting 1,800 patients at baseline and retaining 1,250 patients at 6-month follow-up. Calculations show a minimum of 100 patients per outcome category (risk subgroup) is required for external validation.^42^ Based on our previous studies,^23^–^26^ we anticipate that at least 10% of musculoskeletal patients in primary care will be classified at high risk of poor outcome (the smallest risk stratum), and thus each risk subgroup will include at least 125 follow-up respondents, providing adequate power for validation of the draft Keele STarT MSK tool using data from 6-month follow-up.

### Cohort study analysis

Refining the Keele STarT MSK tool and evaluating its validity will be carried out in four stages. First, the performance of the draft tool will be described. Patients will be classified, using the draft tool (including cutoff points based on the original STarT Back tool, ie, total score <4, “low risk”; total score ≥4 and psychosocial subscale score <4, “medium risk”; total score ≥ 4 and psychosocial-subscale score ≥4, “high risk”), as being at low, medium, or high risk of poor outcome.^23^ They will be described in terms of their baseline characteristics: pain (pain intensity, pain interference, pain bother), physical function (SF-36 version 2 physical component score [PCS]), mental health (SF-36 version 2 mental component score), general health (SF-36 version 2, sleep problems, fatigue, physical activity, comorbidity), psychological reactions to pain (coping strategies, pain self-efficacy, illness perceptions), quality of life (EQ-5D-5L), health literacy (single-item literacy screener), and social factors (eg, available emotional and instrumental social support, employment status, socioeconomic status). This will allow assessment of the draft tool’s discriminant validity, ie, ability to discriminate between low-, medium-, and high risk subgroups. Hypotheses will be tested based on the assumption that participants in medium- and high-risk subgroups will have higher pain intensity,^54^ more pain bother, poorer physical function, and lower levels of physical and mental health. Evaluation will be based on analysis of variance using linear constraints for numerical measures and the *χ*^2^ test for trends for comparing and testing associations in categorical outcome measures. In order to assess construct validity, risk subgrouping based on the draft tool will be compared with classification based on the Örebro Musculoskeletal Pain Screening Questionnaire,^20^ an existing tool for the prognostic classification of patients with musculoskeletal conditions (medium and high scores will be combined for purposes of this comparison). In the subsample of participants with low-back pain, comparisons will also be made with risk classification according to the STarT Back tool. The results will be expressed as percentage agreement and weighted *k*-values with 95% confidence intervals. Test of linear association will also be given by the *χ*^2^ test for trend.

The predictive performance of the draft Keele STarT MSK tool will be investigated by assessing the ability of the tool to predict outcome at the 2-month follow-up. It is hypothesized that participants with lower baseline scores (ie, those at “low” risk (or “medium” risk compared to “high” risk) will have better outcomes. Evaluation will be based on analysis of variance using linear constraints for numerical 2-month measures, and the *χ*^2^ test for trends for comparing and testing associations in categorical 2-month outcome measures. In relation to the key outcomes of physical health (SF-36-PCS), predictive performance of the draft tool will be expressed in terms of percentage of variance explained (parametric and nonparametric Nagelkerke *R*^2^), calibration (calibration slope and Hosmer–Lemeshow test), and area under the receiver-operating characteristic curve (*C*-statistic) via receiver-operating-characteristic analysis for discrimination, including dichotomies for the SF-36-PCS based on lower tertiles extracted from a similar cohort,^26^ ie, 37.17 and 39.61 at 2- and 6-month follow-up, respectively.^55^,^56^ A replication of this analysis using the SF-36-PCS will be carried out for pain intensity (eg, a score of 5 or more denotes moderate/severe pain).^57^ In addition, as a sensitivity analysis, variation in performance will be examined across participants with different index pain sites.

Second, opportunities to refine and improve upon the draft Keele STarT MSK tool will be investigated. In particular, face and content validity, completion rates, and predictive performance of the tool will be optimized by the inclusion of additional or alternative items or the removal of items. Predictive performance will be assessed against physical health (SF-36-PCS) and pain-intensity scores at 2-month follow-up. Primary evaluation will use the whole sample, but sensitivity analyses will be carried out for participants with pain at each index site. A number of single-candidate item questions will be included in baseline questionnaires (physical, psychological, or social factors); these are based on an updated review of prognostic factors for musculoskeletal pain in primary care, overview of other comparable tools (Örebro and Von Korff risk score), and examination of other questions used to measure the same and/or other identified key domains. As with the development of the Keele STarT Back tool,^23^ all candidate items will be potentially modifiable by treatment. This analysis will be carried out in stages by substituting, adding, or removing one item at a time. Decisions about whether to change, add, or remove an item will be based on all available information (face and content validity, item-completion rate, and predictive performance overall and across pain sites). For example, if swapping one item in the draft tool for a new candidate item with better face validity leads to similar item-completion rates and improves predictive performance compared to the draft tool, a decision would be made to remove the existing item and add the new item.

The refined tool will then be investigated to see whether it is exhaustive by checking whether items reflecting different domains can be added to improve predictive validity substantially. In addition, the potential for item redundancy will be examined by reviewing the tool’s predictive performance versus simplification by exclusion of single items one at a time. At all stages, the main focus will be on improved predictive performance across the total study population, but review of predictive validity will also be extended to individual index pain sites, and face and construct validity will be taken into account.

The third step is to identify tool risk-strata cutoff points. Two approaches will be considered. One approach will identify the optimal cutoff points on the 0–9 scale that stratifies the population into three subgroups of low, medium, and high risk based on evaluation of sensitivity/specificity, predictive values (positive/negative), and likelihood ratios (positive/negative) against clinical thresholds for the SF-36-PCS and pain, as detailed earlier. An alternative method used in the development of the STarT Back tool^23^ is based on a separate cutoff point using a psychosocial subscale to identify complex patients. In this approach, items that could be classified as key in identifying patients who are at high risk (ie, psychosocial, complex problems) will be identified. These two approaches to defining cutoff points will be compared in terms of discriminant, construct, and predictive validity (as described in steps 1 and 2) and reviewed by the study team for feasibility and fit.

The fourth and final stage is to determine whether the refined version of the tool has external validity. This will be done by assessing the discriminant, construct, and predictive validity of the refined tool against 6-month outcomes. In addition, these same analyses will be conducted following multiple imputation of missing data to assess robustness of the tool’s properties. At all stages of the analysis, a clinical advisory group and user representatives (patient and public involvement of people with similar musculoskeletal conditions) will be consulted about the draft versions of the Keele STarT MSK tool, and any suggested changes will be discussed, to ensure acceptability, face validity, and clinical utility of the final screening tool, cutoff points, and identified risk strata.

Current health care and treatments for the whole cohort by risk strata and by pain site will be described using data from patient self-report questionnaires at 6 months. NHS and non-NHS resource use will be multiplied by unit costs obtained from standard sources, in order to calculate mean overall per patient costs and by broad health care-resource use type. A description of mean costs by risk strata and by pain site will be presented. Responses to the EQ-5D-5L will provide estimates of mean quality of life (utility) values, again for the whole patient group and by risk strata and pain site.

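### Stage two picks tool items on apparent 2-month prediction with no allowance for sampling error, so the refined tool's gain over the draft tool will be optimistic

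*Protocol article*

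**What the plan says.** The point sits in the Protocol article, Cohort study analysis, second stage (refining the draft tool).

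- The pool of alternatives is open-ended: "A number of single-candidate item questions will be included in baseline questionnaires". Their number is not stated.
- The search is stepwise: "This analysis will be carried out in stages by substituting, adding, or removing one item at a time". Prediction is judged on SF-36-PCS and on pain intensity at 2 months.
- The general basis for a decision is broad: "Decisions about whether to change, add, or remove an item will be based on all available information", listed as "face and content validity, item-completion rate, and predictive performance overall and across pain sites".
- A swap is then illustrated. The candidate must be the better one on face validity; if the exchange then "leads to similar item-completion rates and improves predictive performance compared to the draft tool, a decision would be made to remove the existing item", the candidate takes its place.
- For items added later, the wording includes a size, though without a number: "checking whether items reflecting different domains can be added to improve predictive validity substantially".
- The same stage says that the principal emphasis throughout is better prediction in the whole sample.

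The fourth stage re-assesses the refined tool against 6-month outcomes. A clinical advisory group and user representatives are consulted at every stage.

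**The concern.** Of the three conditions in the swap example, only the predictive one uses outcome data, and it is met by any observed improvement. Two items of equal true value will almost never show identical observed performance, so this condition alone cannot separate a better item from a lucky one. The data that choose the item also measure its gain, so the 2-month performance of the refined tool, and its advantage over the draft tool, are estimated after selection in the selecting sample.

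At stake is how far the reported improvement can be believed. The cutoff points in stage three are built on the chosen items, and stage four tests them in the same patients with the same baseline answers. A chance advantage at 2 months can therefore partly reappear at 6 months and look like confirmation.

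**Working it through.** **The plan's own figures.** The article gives no error rate or expected gain for the swap step. Its sample figures reproduce: 3,000 × 0.60 = 1,800 recruited, and 0.10 × 1,250 = 125 in the smallest stratum. The number with 2-month data is not stated; 1,250 to 1,500 is assumed below. A nine-item tool is assumed from the 0–9 scale in stage three.

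**One equally predictive candidate.** The difference in observed performance is symmetric about zero, so P(gain > 0) = 0.50. Simulation (nine binary items, n = 1,400, AUC about 0.77–0.78, latent item correlation 0.3 or 0.5, 600 runs each) gave 0.46–0.49. If both outcomes had to improve, it gave 0.29–0.32.

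**Several equally predictive candidates for one item.** The k candidates share a comparator, so the existing item is best with probability 1/(k + 1). At least one candidate passes with probability k/(k + 1). The independence formula 1 − 0.5^k would overstate this.

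| k | k/(k + 1) | simulated, one outcome | simulated, both outcomes | 1 − 0.5^k |
|---|---|---|---|---|
| 3 | 0.75 | 0.74–0.75 | about 0.56 | 0.88 |
| 5 | 0.83 | 0.81–0.82 | 0.66 | 0.97 |
| 10 | 0.91 | 0.89–0.90 | 0.77–0.78 | 0.999 |

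All these figures take the face-validity and completion conditions as already met, so they are upper limits for the example as written.

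**Size of the false gain at 2 months.** The SD of a single-swap AUC difference was 0.003–0.004 in the simulation above. It was about 0.0046 in a second one (true AUC 0.738, 34% poor outcome, N = 1,250 or 1,500). If a swap is kept only when the difference is positive and the true difference is zero, the mean apparent gain per item tried is SD × 0.399.

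- SD 0.0041: 0.0041 × 0.399 = 0.0016 for one item. Three items give 3 × 0.0016 = 0.005, and nine give 9 × 0.0016 = 0.015.
- SD 0.0046: 0.0046 × 0.399 = 0.0018 for one item. Three items give 0.0055, and nine give 0.017.
- Simulating nine matched one-at-a-time swaps directly gave 0.0145–0.0152, with 4.3–4.4 items swapped on average.
- When candidates compete for one item only, the best of ten equal candidates showed a mean gain of 0.003–0.004.

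The true gain is zero in every case.

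**Carry-over to 6 months.** With n = 1,250, nine matched candidates and an apparent 2-month gain of 0.015, the same patients still showed a false gain of 0.005 at 6 months when the residual 2-/6-month outcome correlation was 0.4, and 0.008 when it was 0.7. Both correlations are assumed.

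**Slightly weaker candidates.** For a true loss of 0.002 per swap, P(observed gain > 0) = P(Z > 0.002/0.0046) = P(Z > 0.43) = 0.33. Simulation gave 30–38%.

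**The case against.** The strongest reply is that the article sets no mechanical rule. The swap is introduced as an example. It also requires better face validity and similar completion, and the sentence before it rests decisions on all the evidence, including results by pain site. This stands. A reader might infer that any apparent gain is accepted, but in the example a gain is necessary and not sufficient.

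A reader might also infer that some refinement is almost certain. That is not supported. The number of candidates is unknown, and near-certainty needs many candidates that pass the judgement conditions and are spread over several items, or freedom to replace any of nine equal items on prediction alone. Nor does the text say that each accepted change becomes the new reference; it names the draft tool as comparator. The nine-swap figure is therefore a scenario.

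Second, an equally predictive item with better face validity does no harm. This also stands for the tool itself, but not for the claim that prediction improved. For slightly weaker items there is a small true loss.

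Third, requiring a larger gain for additions than for swaps has a reason: an addition lengthens the tool. The difference in wording is not an inconsistency.

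Fourth, a threshold may sit in an analysis plan that is not shown. That is possible, and a missing number alone would be no finding. But the article itself states the criterion and what follows from meeting it, and this selection step inflates the reported performance unless a correction is made.

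Fifth, stage four and the advisory groups offer a check. The 6-month test is in the same people, so it removes only part of the optimism. The advisers are consulted on acceptability, face validity and utility, which does not reveal chance gains.

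**Conclusion.** The concern holds in a limited form. Items are selected on apparent 2-month performance, and the swap example asks only for an observed improvement among candidates that pass the judgement conditions. On one outcome, an equally predictive candidate passes that part about half the time. The resulting optimism in the refined-minus-draft AUC is modest: about 0.002–0.005 for one to three matched swaps and about 0.015 if nine are tried, of which perhaps 0.005–0.008 would persist at 6 months. These sizes rest on assumed candidate numbers, item correlations, 2-month sample size and outcome correlation.

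The documents do not show that the refined tool would be materially worse than the draft tool, or that item content would be decided by noise alone. What they support is that the reported 2-month improvement would be too favourable, and that the 6-month results are not an independent check on it.

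**What to change.** In Cohort study analysis, second and fourth stages:

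1. Repeat the predictive selection step (swap, add, remove, among candidates that have passed the face-validity and completion judgements) within each bootstrap sample.
2. Report the optimism-corrected C-statistic and R² of the refined tool, and its optimism-corrected difference from the draft tool with a paired interval in the same patients.
3. Where an item is replaced for face validity without a clear predictive gain, say so and do not claim improved prediction.

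A hard acceptance threshold is optional, because each version has a price. Requiring a one-sided 97.5% lower bound above zero would pass an equal item about 2.5% of the time for one candidate and about 15% for ten, but would also block many useful swaps. Allowing a face-validity swap if the 95% interval excludes an AUC loss above 0.01 means accepting observed changes above −0.01 + 1.96 × 0.0046 = −0.001. That passes an equal item about 59% of the time and one truly worse by 0.002 about 41%, so it does not screen out chance.

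The cost is plan wording and computing time, with no new data. The reported gain will be smaller. The judgement-based part of the selection cannot be bootstrapped, so the correction is partial and should be described as such.
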